### Plan for statistical analysis

We will present the incidence of serious adverse events by group at 30 days postoperative and calculate a risk difference and relative risk with 95% confidence intervals around the estimates. The mean and standard deviation for all continuous outcomes (Satisfaction, WOMAC, SF-12, HHS, Pain NRS, and CAS) will be calculated for each group at each time point and calculate the mean between-group difference with 95% confidence interval. Linear mixed models, using a covariance structure that allows for correlations between measurements to decline as they are further apart in time will be used to evaluate improvements in function after surgery since this provides a powerful approach to analyze complex longitudinal data while controlling for important covariates such as gender, comorbidities, age and surgeon/site. All data will be analyzed according to the intention-to-treat principle with an as treated analysis also performed.

We will conduct a cost-effectiveness analysis from both a Canadian healthcare payer and societal perspective using the incidence of adverse events as our effectiveness outcome to estimate cost-effectiveness at 3 months postoperative. We will determine cost-effectiveness using the net benefit regression (NBR) framework to estimate the incremental net benefit (INB) of outpatient arthroplasty [22]. An intervention is considered to be cost-effective if the INB is greater than zero. NBR also provides a means to adjust for potentially confounding factors and therefore allows greater statistical efficiency and a more precise estimate of the INB. To characterize the statistical uncertainty around our estimate of INB we will calculate 95% confidence intervals, and a cost-effectiveness acceptability curve [23].

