### Participant timeline

Patients will be screened and consent obtained at the time of booking for surgery and baseline assessments will occur at the preoperative visit within 3 months of surgery. On the day of discharge from hospital, we will obtain a pain score from participants and provide them with a daily diary to record costs for the first 2 weeks. Postoperatively, participants will be seen at 2 weeks, 6 weeks and 3 months for follow-up.

We will ask caregivers to complete questionnaires preoperatively and at 2 weeks postoperatively (Table 2).

**Table 2 Tab2:** Participant Timeline

Assessments	Appointment				
	Baseline	Discharge	2 weeks	6 weeks	3 months
Demographics	X	–	–	–	–
Charlson Comorbidity Index	X	–	–	–	–
Self-Efficacy	X	–	–	–	–
Pain Catastrophizing Scale	X	–	–	–	–
Expectation Questionnaire: Preop	X	–	–	–	–
Surgical Information Form	–	X	–	–	–
Patient Flow	–	X	–	–	–
Pain NRS	X	X	X	X	X
SF-12v2	X	–	X	X	X
EQ-5D-5L	X	–	–	X	X
WOMAC	X	–	–	–	X
HHS	X	–	–	–	X
Adverse Event Form	–	X	X	X	X
Patient Satisfaction	–	–	X	–	–
Daily Diary	–	–	X	–	–
Patient Satisfaction and Expectations	–	–	X	X	X
Cost Questionnaire	–	–	X	X	X
Caregiver Demographics	X	–	–	–	–
Caregiver Assistance Scale	X	–	X	–	–
Caregiver Strain Index	X	–	X	–	–

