#### Allocation (sequence generation)

All participants will be randomized by the research assistant using a 1:1 ratio for inpatient to outpatient. Randomization will be stratified by surgeon and previous experience with THA (had a THA on the contralateral limb or were the caregiver for someone whom had a THA). All patients will be analyzed according to the treatment group as assigned regardless of when they were discharged.

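### The visit-by-visit mean differences are stated without the baselines that are collected, and the covariate list does not name one of the two stratification factors

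*Protocol article*

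**What the plan says.** All statements are from the Protocol article.

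- **Randomization** (Allocation): "Randomization will be stratified by surgeon and previous experience with THA". Previous experience is entered before allocation, so it is known for every patient.
- **Primary outcome** (Plan for statistical analysis): the plan is to "calculate a risk difference and relative risk with 95% confidence intervals around the estimates". Neither stratification nor adjustment is mentioned.
- **Continuous outcomes** (same section): means and standard deviations by group and visit for satisfaction, WOMAC, SF-12, HHS, Pain NRS and CAS; then "calculate the mean between-group difference with 95% confidence interval". No baseline term is mentioned.
- **Mixed models** (same section): these "will be used to evaluate improvements in function after surgery", "controlling for important covariates such as gender, comorbidities, age and surgeon/site".
- **Economic analysis** (same section): "NBR also provides a means to adjust for potentially confounding factors", with no covariates named.
- **Schedule** (Table 2): baselines exist for WOMAC and HHS (then 3 months), SF-12 (then 2 weeks, 6 weeks and 3 months), Pain NRS (then every visit) and CAS (then 2 weeks). Satisfaction has no baseline score.

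**The concern.** A difference in raw follow-up means leaves two things in the estimate that a baseline-adjusted difference removes: chance imbalance at baseline, and the part of the outcome variance that baseline predicts. Five of the six listed outcomes have the baseline needed. The interval stated for them is therefore wider than it has to be, to the extent that baseline and follow-up are correlated.

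The second point is a mismatch between design and analysis. Surgeon and previous THA experience drove the allocation. The covariate list names surgeon/site together with three factors that did not drive it (gender, comorbidities, age), but not previous experience. Where stratification factors predict outcome, an analysis that leaves them out gives standard errors slightly too large for the design.

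At stake is precision on the secondary outcomes and, to a very small degree, on the non-inferiority comparison. Bias is not at issue.

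**Working it through.** **1. The plan's own sample size.** Inputs from the Sample size section: risk 8% in both arms (the case that gives the maximum), margin 6 percentage points, one-sided 5%, power 80%.

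n per arm = (1.645 + 0.842)² × 2 × 0.08 × 0.92 / 0.06² = 252.8, rounded up to 253, so 506 in total. This matches the stated figure. It uses an unadjusted variance, so the sample size does not depend on any covariate adjustment.

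**2. Continuous outcomes.** Let r be the correlation between baseline and follow-up. The article gives no r, so the range is an assumption. Relative to the raw follow-up difference, the ANCOVA variance factor is 1 − r², the interval width factor is √(1 − r²), and the equivalent sample size is 506 / (1 − r²).

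| r (assumed) | Variance factor | Interval narrower by | Equivalent N | Extra patients |
|---|---|---|---|---|
| 0.3 | 0.91 | 5% | 556 | 50 |
| 0.5 | 0.75 | 13% | 675 | 169 |
| 0.6 | 0.64 | 20% | 791 | 285 |

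How baseline enters also matters. If improvement were analysed as a raw change score, with equal variances at both visits, the factor would be 2(1 − r): 1.4 at r = 0.3, 1.0 at 0.5 and 0.8 at 0.6. At each of these values ANCOVA does better.

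**3. Primary outcome.** Expected events per arm: 253 × 0.05 = 12.7 to 253 × 0.08 = 20.2.

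Let R² be the share of the binary variance explained by the strata. The crude standard error is √(2 × 0.0736 / 253) = 0.0241. The true one under stratified allocation is this times √(1 − R²).

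- Power of the crude test: Φ[(0.06 − 1.645 × SE crude) / SE true].
- Power of the stratified test: Φ[0.06 / SE true − 1.645].

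Assumptions, none of them in the article: six surgeons, 30% with previous experience, overall risk 8%.

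| Range of stratum risks | R² | Power, crude | Power, stratified | One-sided type I error, crude |
|---|---|---|---|---|
| 4.4 to 11.7% | 0.6% | 80.1% | 80.2% | 4.96% |
| 2.7 to 14.4% | 1.6% | 80.2% | 80.6% | 4.90% |
| 1.8 to 17.8% | 3.2% | 80.4% | 81.1% | 4.80% |
| 0.9 to 21.5% | 5.4% | 80.7% | 81.9% | 4.65% |

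Even with extreme differences between strata, the gain is about 1 power point. The crude test stays just under its nominal 5%. Strata based on site are coarser than strata based on surgeon, so they can explain no more than this.

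**4. Sparseness.** Both arms together give about 25 to 40 events. Six assumed surgeons by two experience levels make 12 strata, or 2.1 to 3.4 events per stratum on average. The two sites by two experience levels make 4 strata, or 6.3 to 10.1.

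**The case against.** The strongest reply is that this is a condensed article, and that the estimator, the full covariate list and the ANCOVA terms normally belong in an analysis plan that is not shown. Three stronger readings are tempting, and the article supports none of them.

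- *The models leave out previous experience.* The list is introduced as examples, so it is open. The factor is not named, but nothing excludes it.
- *The primary analysis is fixed as crude, and this endangers the trial.* The article never calls the risk difference unadjusted; that would be inferred from silence. Even if it is crude, the interval is valid, slightly conservative, and consistent with the variance behind the 506.
- *Baselines are ignored throughout and every secondary interval is too wide.* Satisfaction has no baseline to use. The mixed models concern improvement in function, and HHS and WOMAC are measured only at baseline and 3 months, so a longitudinal model of them most plausibly already contains the baseline.

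It is also fair to say that surgeon-level strata would be sparse, and that a rule to pool strata once the data are seen would add discretion to a non-inferiority decision.

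What remains is narrower. For continuous outcomes the article does state an estimator, and that estimator has no baseline term. Pain NRS, CAS and SF-12 are not clearly covered by the function models, so for them the visit-by-visit difference is the stated analysis. For HHS and WOMAC the article does not say how baseline enters.

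**Conclusion.** The point holds as an inexpensive improvement in precision and consistency, and it is not an error that threatens validity. It is clearest for Pain NRS, CAS and SF-12. For the five outcomes with a baseline, adjustment would narrow intervals by about 5 to 20%, provided the baseline to follow-up correlation lies between 0.3 and 0.6. That range is an assumption; a weaker correlation would give less. To the extent that the function models already carry baseline, the gain for HHS and WOMAC is already partly or wholly secured.

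For the primary outcome the point is minor. The gain is about 0 to 1 power point under assumed strata, and the reason to act is agreement with the randomization rather than rescue of power.

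**What to change.** 1. For WOMAC, SF-12, HHS, Pain NRS and CAS, state that the reported between-group difference is baseline-adjusted (ANCOVA or mixed model), with the baseline value, surgeon/site and previous THA experience as covariates. Keep raw means and standard deviations by visit as description. Satisfaction can take the same covariates without a baseline.
2. Name previous THA experience next to surgeon/site in the mixed-model covariate list.
3. For the primary outcome, state a risk difference stratified by previous THA experience and site (for example with Mantel-Haenszel weights), and keep the crude difference as a sensitivity analysis. Fix the use of site rather than surgeon in advance, so that no pooling decision depends on the observed events.

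The cost is analysis wording only. Every variable is already collected, the sample size is unchanged, and the article says that recruitment is still under way, so the change can be made before the data are analysed.

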### Patient and public involvement

Patients or the public were not involved in the design, or conduct, or reporting, or dissemination plans of our research.

### Data collection methods

Follow-up assessments for this study coincide with the standard of care follow-up schedule for the surgeons at our centre. During each visit, the research assistant will administer the questionnaires to the participants and ensure they are completed. Alternatively, participants are also given the option to complete questionnaires online by directly accessing the electronic data capture (EDC) system (*Empower Health Research*). The HHS will be completed by the treating surgeon at the three-month visit.

### Data management

Participants have the option to complete questionnaires either in hard copy or using the EDC system (*Empower Health Research*).

## Discussion

This protocol is for a multi-centered randomized controlled trial to assess the safety and cost-effectiveness of outpatient total hip arthroplasty compared to standard inpatient care. There is currently a lack of high-quality studies evaluating the safety and effectiveness of outpatient THA. Most studies that have assessed safety have used US national databases [24–29] or observational cohort designs [30–33] with only one published randomized trial [34]. Previous prospective studies have also been underpowered to detect differences in complication rates between outpatient and inpatient care groups. Due to the already low rates of serious adverse events after THA, reported from 3.8% up to 8.6% in the literature, [20, 35, 36] sample sizes must be sufficiently large to include a sufficient number of events to support clinical conclusions. Our protocol will be the first adequately powered prospective study to evaluate the safety of outpatient THA.

One strength of our study protocol is the use of a modified Zelen consent model [19], as one of the difficulties with assessing outpatient discharge in comparison with standard inpatient care is potential patient biases. This design allows us to avoid these biases as patients with a strong preference for either group are not made aware of the alternative intervention. A weakness of the randomized trial by Goyal et al. (2017) was the lack of blinding which led to a significant number of crossovers due to personal preference [34]. Our use of a modified Zelen consent model [19] should help to address this issue and reduce the number of crossovers in our study. Future studies looking to evaluate outpatient THA should also consider use of this design to strengthen their conclusions and reduce patient crossover.

Our study will be the first to perform a full economic evaluation in conjunction with a large randomized trial and will use both healthcare payer and societal perspectives. No full economic evaluations have been published to compare outpatient to standard inpatient care thus far. This is an important gap in the literature as international health economic guidelines suggest policy and clinical decisions should be supported by evidence produced when cost is evaluated simultaneously with effect in a full economic evaluation [37, 38]. Previous studies have evaluated cost alone [5, 6] and none in conjunction with a prospective trial. These studies have also only included direct costs associated with the procedures and hospital costs. Including a broader perspective and incorporating indirect costs such as time off work and caregiver assistance are important to consider, ensuring that costs possibly saved from reduced hospital stays are not shifted elsewhere in the recovery pathway. To truly know whether outpatient THA is less costly than inpatient care, as the literature currently suggests [5, 6], broader perspectives (ie. healthcare payer and societal) should be assessed. The use of multiple perspectives also helps to broaden the interpretability of study results and is recommended by international health economic guidelines [37]. The importance of costing perspective is highlighted in a paper by Primeau et al. (2019) where the conclusions of the study changed depending on the perspective used [39].

Our protocol hopes to address several gaps in the current literature with a large and adequately powered sample size to assess safety, the use of blinding with a modified Zelen consent model [19], and assessing costs in conjunction with a prospective randomized trial for a full economic evaluation. Conclusions from our study should help to inform clinical decision making in the use of outpatient care programs in standard practice for THA. Recruitment for the study is currently ongoing.

## Data Availability

Not applicable.

## Abbreviations

ASA: American Society of Anesthetists
CAS: Caregiver Assistance Scale
CSI: Caregiver Strain Index
EDC: Electronic data capture
EQ-5D: European Quality of Life Scale
HHS: Harris Hip Score
HRQOL: Health-related quality of life
INB: Incremental net benefit
NBR: Net benefit regression
OA: Osteoarthritis
Pain NRS: Numeric Pain Rating Scale
SF-12v2: 12-Item Short Form Health Survey
THA: Total hip arthroplasty
TKA: Total knee arthroplasty
VAS: Visual analog scale
WOMAC: Western Ontario and McMaster Universities Osteoarthritis Index
